***1. Background and objectives***

Insomnia is one of the common complaints about sleep disorders of maintenance hemodialysis (MHD) patients. To get the desired sleep quality, hypnotic sedative agents are often prescribed at high doses and for long duration, raising risks of all kinds of adverse effects. As a non-drug therapy, auricular acupressure therapy (AA) is attractive to both patients and practitioners and is widely used to treat many conditions in China. However, concerning for its effectiveness in managing insomnia, its evidence base remains poor requiring rigorous high-quality trials.

In view of this, we designed this randomized controlled pilot study to test the hypothesis that auricular acupressure is a feasible and safe method treating insomnia for MHD patients, and to support carrying out rigorous large scale randomized controlled trials in the future.

***2. Flow chart of study procedures:***

Eligible MHD patients with insomnia

Week 1

AA treatment

SAA treatment

Week 8

Follow-up

Follow-up

Week 20

1. ***Study Design***

3.1 ***Study Design*** A double-blinded, randomized sham-controlled pilot study.

***3.2 Participants:*** MHD patients with insomnia.

***3.3 Inclusion criteria***

Subjects are selected MHD patients from local hemodialysis center (Hemodialysis center, Guangdong Provincial Hospital of Chinese Medicine) who are dialyzed twice or three times a week (total treatment time ≥ 10 hours per week). Those meeting all of the following criteria are included:

**·**Age 18~75 years

**·**Under regular maintain hemodialysis treatment for 12 and 120 months

**·**Chronic primary insomnia according to DSM-IV-TR，and PSQI global score > 7

**·**Independent of hypnotics, or using a minimal maintaining dose of hypnotics (e.g. estazolam≤1mg/d), during the last three months

**·**Informed consent.

***3.4 Exclusion criteria***

Patients with any of the following conditions are excluded:

**·**Presence of co-morbidities (e.g. cancer, congestive heart failure, connective tissue disease, hematologic diseases) and of psychiatric disorders;

**·**Inadequately dialyzed, indicating by urea clearance index (KT/V) lower than 1.20;

**·**Presence of severe physical symptoms such as bone pain and itchy skin, etc., which are obviously causative for insomnia;

**·**Fatigue caused by severe anemia (hemoglobin<60g/L) or malnutrition (serum albumin<30g/L).

***3.5 Randomization, allocation and Sample size***

A random sequence will be produced using computer software (Microsoft Excel 2003) and kept by an investigator who is not involved in running the trial. Eligible participants are randomly allocated into either AA group or Sham AA (SAA) group.

As a pilot study, sample size calculation was not performed. A sample size of 60 subjects is going to collect at a ratio of 1:1.

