***8. Outcome measurements***

8.1 PSQI score: The sleep quality will be evaluated at baseline, end of treatment (week 8), 4 weeks (week 12), 8 weeks (week 16) and 12 weeks (week 20) after treatment.

8.2 Clinical and laboratory parameters [including serum creatinine (SCr), blood urea nitrogen (BUN), total carbon dioxide (TCO2), potassium (K+), calcium (Ca2+), phosphate (PO43-), parathyroid hormone (PTH), albumin (Alb), hemoglobin (Hb)]: at baseline, and at the end of follow-up (week 20).

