8.3 The weekly dose of hypnotics

8.4 The clearance rate of urea nitrogen (Kt/V)

**9. *Patient safety***

Clinical and laboratory investigations and adverse events throughout the treatment and follow-up periods will be documented. Measures will be taken immediately to deal with potential adverse events such as fainting, severe pain and local infection, no matter whether they are related to AA. When necessary, the researcher will be informed to break the blindness.

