***11. Statistical analysis***

Missing data will be imputed with the last observation. For dichotomous data, Chi-squared test or Fisher’s exact test will used. For continuous data, t test will be used. Repeated-measures analyses of variance will be conducted to compare changes on PSQI global score and each domain. P value less than 0.05 will be considered statistically significant. Statistical analysis will be processed using SPSS 18.0.

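### Hypnotic use at entry is used in neither the allocation nor the stated tests, which costs precision and interpretability, mainly for weekly hypnotic dose

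*Protocol*

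**What the plan says.** On entry, Protocol 3.3 accepts patients who are "Independent of hypnotics, or using a minimal maintaining dose of hypnotics (e.g. estazolam≤1mg/d), during the last three months". Two kinds of patient, distinguishable at screening, therefore enter the trial.

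On allocation, Protocol 3.5 says: "A random sequence will be produced using computer software (Microsoft Excel 2003) and kept by an investigator who is not involved in running the trial". It continues: "Eligible participants are randomly allocated into either AA group or Sham AA (SAA) group". The size is given as "A sample size of 60 subjects is going to collect at a ratio of 1:1", with no calculation behind it because the study is a pilot. No strata, blocks or minimisation are named.

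On outcomes, item 8.3 reads, in full, "The weekly dose of hypnotics". Items 8.1 and 8.2 give a baseline and later time points for PSQI and the laboratory values; 8.3 gives neither.

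On analysis, section 11 assigns the t test to continuous data. For PSQI it says: "Repeated-measures analyses of variance will be conducted to compare changes on PSQI global score and each domain". No term for hypnotic use at entry appears in either.

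**The concern.** Hypnotic use at entry is known before allocation, is likely to relate to sleep scores, and almost determines the starting value of one listed outcome. A non-user starts at a dose of zero and cannot reduce it; a user can. When such a factor enters neither the allocation nor the comparison, its whole variation goes into the error term. The arms may also differ visibly in their share of users in the one allocation that is carried out.

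At stake are the width of the interval for weekly dose and the ease of reading a between-arm difference in dose. Section 1 says the pilot is meant to support larger trials, so imprecise estimates will be carried forward into planning. The validity of the comparison is not at stake.

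**Working it through.** **Inputs.** From the protocol: 60 patients at 1:1, so 30 per arm (3.5); an example ceiling of 1 mg/d estazolam, which is 7 × 1 = 7 mg/week (3.3). The protocol does not give the share of users, the mean dose of users, or the PSQI difference between users and non-users. These are assumed below and varied. There is no power calculation to reproduce.

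**1. Chance of an uneven share of users, arms fixed at 30:30.** With m users among 60, the number k in one arm is hypergeometric (60, m, 30). A difference of at least 20 percentage points means at least 0.20 × 30 = 6 patients, that is |2k − m| ≥ 6.

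| Users among 60 (assumed) | P(difference ≥ 20 points) |
|---|---|
| 12 | 0.104 |
| 20 | 0.170 |
| 30 | 0.196 |

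The SD of the difference in the share of users is (2/30) × √[30 × (m/60) × (1 − m/60) × (30/59)]. This is 0.104 for m = 12 and 0.130 for m = 30. A difference of 30 points or more is rare, at 0.2% to 1.9% for 12 to 30 users.

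**2. Weekly dose, shift in one allocation.** Assume users take 0.5 to 1 mg/d, which is 3.5 to 7 mg/week. A 20-point imbalance then gives an arm difference, before any acupressure, of 0.20 × 3.5 = 0.7 to 0.20 × 7 = 1.4 mg/week.

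**3. Weekly dose, precision.** Assume doses stay near their entry level, non-users stay at zero, and users are spread evenly over 3.5 to 7 mg/week. Users then have mean 5.25 and variance (7 − 3.5)²/12 = 1.02. With one third users (20 of 60):

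- variance between users and non-users: (1/3)(2/3) × 5.25² = 6.13
- variance within users: (1/3) × 1.02 = 0.34
- SE of the arm difference, plain t test: √(6.13 + 0.34) × √(2/30) = 2.54 × 0.258 = 0.66 mg/week
- SE with the stratum in the allocation and the analysis: √0.34 × 0.258 = 0.15 mg/week

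With 20% users the same steps give √(4.41 + 0.20) × 0.258 = 0.55 against √0.20 × 0.258 = 0.12. With 50% users they give √(6.89 + 0.51) × 0.258 = 0.70 against √0.51 × 0.258 = 0.18. The gain shrinks if doses move far from their entry values during the trial.

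**4. PSQI change.** If users and non-users differ in change by an assumed 1 to 3 points, a 20-point imbalance shifts the arm difference by 0.20 × 1 = 0.2 to 0.20 × 3 = 0.6 points. With an assumed SD of change of 2 to 4 points, the SE of the arm difference is SD × √(2/30), about 0.5 to 1.0. A mid-range shift of 0.4 lies within one SE.

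**5. After stratification.** With an assumed block size of 4, the arms can differ by at most 2 users, 2/30 or about 7 points.

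**The case against.** The strongest reply is that chance imbalance after proper randomisation is random error. Averaged over allocations the shift is zero, and the type I error of the test already allows for it. This stands in full. A reader might infer that uneven hypnotic use would confound or bias the trial; nothing in the protocol supports that, since allocation is random.

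A reader might also infer that a single sequence fails to secure the 1:1 ratio. Section 3.5 does not say that each patient is allocated by an independent coin toss. A shuffled list of 30 AA and 30 SAA labels fits its words and gives exactly 30:30. The chances in step 1 are for that fixed split. Under coin-toss allocation the chance of a 20-point difference would be about 6% to 16%, and the two sets of figures are alternatives.

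Four further points carry weight. Leaving a single-centre pilot of 60 unstratified is a legitimate choice and contradicts nothing in the protocol. PSQI is analysed as change from a measured baseline, which removes part of any entry difference. Users are limited to a minimal maintenance dose and all patients must score above 7 on the PSQI, which narrows the contrast. Covariates are commonly left to a statistical analysis plan, which is not shown here, and adjustment alone would deal with much of the problem.

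The last point does not remove the concern. The allocation scheme has to be fixed before the first patient, and a later analysis plan can adjust but cannot stratify. Section 11 also commits itself to a plain t test for continuous data, and 8.3 states no baseline for dose.

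**Conclusion.** The point holds as an inexpensive improvement, not as a flaw that invalidates the comparison. The loss is in precision and interpretability and falls mainly on weekly hypnotic dose. Under the assumptions in step 3, the standard error there could fall from about 0.66 to 0.15 mg/week. With arms of 30:30, an imbalance of at least 20 points in users has a chance of about 10% to 20% for an assumed 12 to 30 users. The effect on PSQI change is smaller, about 0.2 to 0.6 points in an allocation with a 20-point imbalance. All these sizes rest on assumed shares, doses and PSQI differences that the protocol does not give. That no stratification, no adjustment term and no baseline for dose are stated is plain from sections 3.5, 8.3 and 11.

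**What to change.** In 3.5, state that allocation uses permuted blocks of randomly varying size, stratified by hypnotic use at entry (yes/no), with the lists still held by the uninvolved investigator.

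In section 11, include that stratum in the PSQI and weekly-dose comparisons. For weekly dose, preferably include the dose at entry as well, and record that dose at baseline under 8.3. Both parts are needed: if the allocation is stratified but the plain t test is kept, the test still charges the user/non-user variation to error and becomes conservative.

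The cost is one extra allocation list, prepared before the first patient, and slightly more analysis work. If recruitment has already begun, the adjustment in section 11 can still be adopted before unblinding and recovers most of the gain.

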***6. Interventions***

***6.1 Co-intervention***

All patients maintain regular hemodialysis using dialysis machine from Fresenius Medical Care Co.Ltd. and B.Braun Co.Ltd. Reverse osmosis water is applied. For each treatment, we use disposable dialyzers with well biocompatibility and bicarbonate dialysate in a flow rate of 500ml/min. Blood flow rate is set at 180ml/min. Either unfractionated heparin (UFH) or low molecular weight heparin (LMWH) is used to prevent coagulation. Patients receive 2-3 hemodialysis sessions every week, each for 4 hours. Their Kt/V should be over 1.20, TACurea less than 17.9mmol/L，PCR more than 1.0 to1.2 and URR over 60％, indicating satisfactory dialysis sufficiency. Other agents such as anti-hypertensive drugs, erythropoietin, and iron supplements are administered according to related guidelines.

***6.2 Auricular acupressure intervention***

***Treatment group***

Participants in the treatment group will received AA on five active acupoints including

Acup.1A. *Shen Men* (*Spiritual Gate*, TF4),

Acup.2A. *Jiao Gan* (*Sympathetic autonomic*, AH6a),

Acup.3A. *Xin* (*Heart*, CO15),

Acup.4A. *Pi Zhi Xia* (*Subcortex,* AT4),

Acup.5A. *Nei Fen Mi* (*Endocrine*, CO18).

***Control group***

Participants in SAA group received auricular acupressure on Helix points (HX 5-9), which were clearly remote from the inner ear area.

Acup.1B. Gang Men (HX5)*,*

Acup.2B. Er Jian Qian (HX6),

Acup.3B. Er Jian Hou (HX7),

Acup.4B. Jie Jie (HX8),

Acup.5B. Lun yi (HX9).

***7. Treatment duration and follow up duration***

Treatment period: 8 weeks

Follow up period: 12 weeks following end of treatment.

***8. Outcome measurements***

8.1 PSQI score: The sleep quality will be evaluated at baseline, end of treatment (week 8), 4 weeks (week 12), 8 weeks (week 16) and 12 weeks (week 20) after treatment.

8.2 Clinical and laboratory parameters [including serum creatinine (SCr), blood urea nitrogen (BUN), total carbon dioxide (TCO2), potassium (K+), calcium (Ca2+), phosphate (PO43-), parathyroid hormone (PTH), albumin (Alb), hemoglobin (Hb)]: at baseline, and at the end of follow-up (week 20).

8.3 The weekly dose of hypnotics

8.4 The clearance rate of urea nitrogen (Kt/V)

**9. *Patient safety***

Clinical and laboratory investigations and adverse events throughout the treatment and follow-up periods will be documented. Measures will be taken immediately to deal with potential adverse events such as fainting, severe pain and local infection, no matter whether they are related to AA. When necessary, the researcher will be informed to break the blindness.

**10. *Withdrawal and drop out***

All participants have a right to withdraw from the trial at any time. Any subjects who failed to complete the entire observation are drop-out cases, regardless of the time or reason.

Researchers will contact these patients and attempt to obtain additional information, including the reason for dropping out and the last time they receive treatment. If there were any correlation to adverse effect of drugs or treatments, it should be documented in case report form and reported to researchers. Withdrawal and drop out cases are also reported and analyzed.

***11. Statistical analysis***

Missing data will be imputed with the last observation. For dichotomous data, Chi-squared test or Fisher’s exact test will used. For continuous data, t test will be used. Repeated-measures analyses of variance will be conducted to compare changes on PSQI global score and each domain. P value less than 0.05 will be considered statistically significant. Statistical analysis will be processed using SPSS 18.0.

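### Last-observation imputation gives zero PSQI change to anyone without a week-8 score and can carry the end-of-treatment score through follow-up; the bias depends on dropout and waning

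*Protocol*

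**What the plan says.** - **Missing data (Section 11).** "Missing data will be imputed with the last observation". No other method and no sensitivity analysis is given. The completed data go into t tests and a repeated-measures ANOVA of the PSQI global score and its domains, at a 0.05 significance level.
- **PSQI schedule (Section 8.1).** Sleep quality is "evaluated at baseline, end of treatment (week 8), 4 weeks (week 12), 8 weeks (week 16) and 12 weeks (week 20) after treatment". Nothing is measured between baseline and week 8.
- **Periods (Section 7).** "Treatment period: 8 weeks"; "Follow up period: 12 weeks following end of treatment". Weeks 12, 16 and 20 are therefore all off treatment.
- **Dropouts (Section 10).** "Any subjects who failed to complete the entire observation are drop-out cases, regardless of the time or reason". They stay in the analysis: "Withdrawal and drop out cases are also reported and analyzed". Researchers will try to obtain further information from them, "including the reason for dropping out and the last time they receive treatment". PSQI is not named there.
- **Size (Section 3.5).** 60 participants, 1:1, with no sample size calculation. No SD, expected effect or dropout rate is stated.

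**The concern.** Last-observation imputation can only carry what was measured. On this schedule that means three different things, depending on when a participant is lost:

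- **No week-8 PSQI:** baseline fills weeks 8, 12, 16 and 20. Change is exactly zero throughout, and because entry requires a global score above 7 (Section 3.3) the carried score is always above 7.
- **Lost between weeks 8 and 12:** the end-of-treatment score fills all three follow-up visits, which assumes no waning after treatment stops.
- **Lost after week 12 or week 16:** an off-treatment score is carried for the remaining visits.

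At stake are the week-8 comparison, which then depends on who dropped out as well as on the treatment, and the follow-up comparison, which is meant to show whether any benefit lasts. The aim in Section 1 includes supporting later large trials, so a distorted PSQI comparison matters even in a pilot.

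**Working it through.** The protocol has no figure of its own to reproduce. From the documents: 30 per arm, the visit schedule, the imputation rule and alpha 0.05 (taken as two-sided). Assumed: SD of change 3 (for example SD 3 at each visit with correlation 0.5, since 3 × √(2 × (1 − 0.5)) = 3), the mean changes and dropout rates below, and dropout independent of outcome. Negative change is improvement.

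**1. Week 8, expected difference.** With early dropout d and true mean change μ, the imputed arm mean is (1 − d)μ, so the difference is (1 − d_AA)μ_AA − (1 − d_SAA)μ_SAA.

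| True change AA / SAA | Dropout AA / SAA | True difference | Imputed difference |
|---|---|---|---|
| −4 / −2 | 20% / 20% | −2.0 | 0.8 × (−4) − 0.8 × (−2) = −1.6 |
| −3 / −3 | 20% / 20% | 0 | 0 |
| −3 / −3 | 5% / 10% | 0 | −3 × (0.95 − 0.90) = −0.15 |
| −3 / −3 | 7% / 20% | 0 | −3 × (0.93 − 0.80) = −0.39 |
| −3 / −3 | 20% / 7% | 0 | +0.39 |
| −3 / −3 | 10% / 30% | 0 | −3 × (0.90 − 0.70) = −0.60 |

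**2. Type I error of the week-8 t test.** The imputed variance per arm is (1 − d)·SD² + d(1 − d)μ².

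- 7% v 20%: variances 0.93 × 9 + 0.0651 × 9 = 8.96 and 0.80 × 9 + 0.16 × 9 = 8.64. SE = √((8.96 + 8.64)/30) = 0.766. Ratio 0.39/0.766 = 0.51. Rejection is about 8%.
- 10% v 30%: variances 8.91 and 8.19, SE 0.755, ratio 0.60/0.755 = 0.79. Rejection is about 12% (up to 13% by simulation).
- 5% v 10%: SE 0.772, ratio 0.15/0.772 = 0.19. Rejection is about 5.4%.
- 20% v 20%: about 5.0% by simulation.

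Analysing observed values only is unbiased in these scenarios, with error of about 5%.

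**3. Power, true changes −4 and −2, 20% dropout per arm.**

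- No dropout: about 72%.
- Observed cases only: about 61%.
- Last-observation imputation: variances 0.8 × 9 + 0.16 × 16 = 9.76 and 0.8 × 9 + 0.16 × 4 = 7.84. SE = √(17.6/30) = 0.766. Ratio 1.6/0.766 = 2.09. Power is about 53% to 54%.

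So about 11 points are lost because patients are lost, and about 7 to 8 because of the rule. The second part depends on the arm means: with changes of −2 and 0, imputation gives about 61%, the same as observed cases; with −5 and −3 it gives about 49%.

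**4. Week 20, loss between weeks 8 and 12.** With fraction p lost in that interval and none earlier, the imputed arm mean is p·μ8 + (1 − p)·μ20. Suppose AA goes from −4 at week 8 back to −2 at week 20, and SAA stays at −2, so the true week-20 difference is 0.

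- p = 10%: AA = 0.1 × (−4) + 0.9 × (−2) = −2.2, SAA = −2.0, difference −0.2.
- p = 20%: AA = 0.2 × (−4) + 0.8 × (−2) = −2.4, difference −0.4.

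If the effect truly persists (−4 and −2 at week 20), the same losses leave the difference at −2.0. Early loss of 20% per arm would instead shrink it to −1.6.

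**The case against.** Several stronger readings are tempting, and the protocol does not support them.

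- **That every loss after week 8 carries an end-of-treatment score.** Section 8.1 has off-treatment PSQI at weeks 12 and 16, so this applies only to losses before week 12.
- **That everyone who stops treatment is set to zero change.** Section 10 defines a dropout by incomplete observation. Someone who stops pressing the beads but attends at week 8 has an observed score.
- **That Section 10 ends PSQI collection.** Its list of information to seek is open-ended. It is silent on PSQI and does not rule it out.
- **That the rule favours AA.** The sign reverses if AA loses more patients, and there is no week-8 bias with equal dropout and equal change.
- **That treating imputed values as observed inflates error in itself.** For the week-8 t test with equal dropout and no true difference, type I error stays at about 5%. The inflation shown comes from unequal dropout.
- **That the whole fall from 72% to about 53% is the rule's doing.** More than half of it is lost patients.

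The pilot status is also a fair point. The stated hypothesis is feasibility and safety, nothing is powered, and the protocol does not say that a PSQI effect size or SD will be passed to a later trial. This lowers the severity. It does not remove the point, because Section 11 plans formal tests at 0.05 and Section 1 says the study is to support larger trials. Nor is this a detail left to an unseen analysis plan: the protocol itself states the rule.

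**Conclusion.** The concern holds in a conditional form. The mechanism follows from Sections 7, 8.1, 10 and 11 alone. Its direction and size depend on dropout, arm changes and waning, none of which the protocol gives. Under the stated assumptions the rule removes a fifth of a true 2-point difference at 20% dropout per arm. It produces a false difference of 0.39 to 0.60 points, with type I error of about 8% to 12%, when dropout differs by 13 to 20 percentage points. At 5% v 10% the effect on error is negligible. With 30 per arm, 7% v 20% is about 2 v 6 participants, so a material imbalance needs few people. A falsely lasting benefit of 0.2 to 0.4 points at week 20 arises only if the AA effect has worn off and 10% to 20% are lost between weeks 8 and 12. This should be fixed, but it does not invalidate the trial.

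**What to change.** **Section 11:** replace the imputation sentence with:

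> PSQI at weeks 8, 12, 16 and 20 will be analysed by a likelihood-based mixed model for repeated measures using all observed data from all randomised participants, without single imputation (valid if data are missing at random); last-observation imputation will be used only as a sensitivity analysis.

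**Section 10:** add:

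> PSQI at the remaining scheduled visits will still be sought from consenting participants who stop AA or SAA, where they remain on dialysis at the centre.

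The second change matters because the mixed model relies on missingness at random, and observed scores reduce that reliance. Retrieval is feasible for those still attending two or three dialysis sessions a week, but not for deaths, transplants or transfers. The model removes the built-in zero-change assumption; it does not restore the power lost with the patients.

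Cost: two sentences, no extra participants and no extra visits. The analyst should confirm that the named SPSS version fits the model.

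### Section 11 compares PSQI without baseline PSQI as a covariate, so its valid analyses are less precise than the data allow

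*Protocol*

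**What the plan says.** Section 11 fixes the methods by name. For continuous outcomes: "For continuous data, t test will be used". For PSQI: "Repeated-measures analyses of variance will be conducted to compare changes on PSQI global score and each domain". The significance rule is "P value less than 0.05 will be considered statistically significant". No covariate, model term or visit is named.

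The baseline value exists for everyone. Section 3.3 makes it an entry condition ("PSQI global score > 7"), and Section 8.1 schedules PSQI at baseline and at weeks 8, 12, 16 and 20. Section 8.2 also measures the laboratory parameters at baseline and week 20.

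On size, Section 3.5 says "A sample size of 60 subjects is going to collect at a ratio of 1:1" and "As a pilot study, sample size calculation was not performed".

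**The concern.** With 30 patients per arm, each estimate of the group difference will have a wide interval. A patient's baseline PSQI normally predicts part of the later score. A t test on the final score leaves that part in the error term. An analysis of changes does use the baseline, but it forces a slope of one, which over-corrects whenever the correlation is below one and the SDs are similar. Estimating the slope, as ANCOVA does, removes the predictable part and no more.

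What is at stake is the width of the interval around the treatment difference. Section 1 presents the study as support for larger trials, and an effect estimate from it is useful for that purpose only as far as it is precise.

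**Working it through.** **The plan's own figure.** The total of 60 cannot be reproduced, because no effect size, SD or power is given. At 30 per arm and two-sided 0.05 (sidedness is assumed), the difference detectable with 80% power without adjustment is (1.960 + 0.842) × √(2/30) = 0.72 SD.

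**Inputs.** From the protocol: 30 per arm, alpha 0.05, baseline and four follow-up visits. Assumed: baseline to follow-up correlation ρ of 0.3, 0.5 or 0.7, equal SDs at all visits, complete data.

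**One visit.** Variance of the group difference, in units of that of the final-score t test:

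- t test on final score: 1
- t test on change: 2(1 − ρ)
- ANCOVA: 1 − ρ²

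The ratio of ANCOVA to the change-score test is (1 − ρ²) / [2(1 − ρ)] = (1 + ρ)/2.

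| ρ | Change | ANCOVA | ANCOVA / final | ANCOVA / change |
|---|---|---|---|---|
| 0.3 | 1.40 | 0.91 | 0.91 | 0.65 |
| 0.5 | 1.00 | 0.75 | 0.75 | 0.75 |
| 0.7 | 0.60 | 0.51 | 0.51 | 0.85 |

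At ρ = 0.5, 60/0.75 = 80, so 60 adjusted patients are worth about 80 unadjusted ones.

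**Cost of estimating the slope.** This multiplies the ANCOVA variance by 1 + 1/56. The ratios become 0.93, 0.76 and 0.52 against the final score, and 0.66, 0.76 and 0.87 against change. Break-even against the final score is ρ² = 1/57, so ρ ≈ 0.13. Break-even against change is ρ = 2 × 56/57 − 1 ≈ 0.96. Between these values adjustment beats both. At ρ = 0.5 the detectable difference falls from 0.72 SD to 0.72 × √0.763 = 0.63 SD.

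**Power at one visit for a 0.5 SD difference** (final / change / ANCOVA): 0.49 / 0.37 / 0.52 at ρ = 0.3; 0.49 / 0.49 / 0.60 at ρ = 0.5; 0.49 / 0.71 / 0.77 at ρ = 0.7.

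**The ANOVA, like for like.** Read literally, its group effect compares the mean change over four visits. If all visits are equally correlated, the variance of the mean change is (1 + 3ρ)/4 + 1 − 2ρ = 5(1 − ρ)/4. Adjusted for baseline, the variance of the four-visit mean is (1 + 3ρ)/4 − ρ² = (1 − ρ)(1 + 4ρ)/4. The ratio is (1 + 4ρ)/5, which gives 0.44, 0.60 and 0.76 before the slope cost. Simulation (3,000 runs per scenario, effect sustained at 0.5 SD) agrees in direction. Power of the group effect on changes against the adjusted average is 52% against 86% at ρ = 0.3, 67% against 87% at ρ = 0.5, and 88% against 94% at ρ = 0.7.

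**Validity.** With no true effect, simulated rejection rates of all the tests, adjusted or not, lay between 0.039 and 0.054.

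**The case against.** Several arguments on the other side are sound and limit the point.

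- **Bias.** A reader might infer that omitting baseline biases the result or leaves chance imbalance uncorrected. It does not. The arms are randomised, the unadjusted tests hold their level, and ordinary chance imbalance is already reflected in their standard errors. The loss is one of efficiency.
- **A missed week-8 target.** A reader might infer that the ANOVA fails to target the end-of-treatment effect. Section 8.1 lists the four follow-up visits without ranking them, and Section 1 states a hypothesis of feasibility and safety. No passage makes week 8 primary, and the planned t test could be applied there.
- **Power of a week-8 contrast.** It is tempting to say that an adjusted week-8 comparison beats the planned ANOVA. That depends on how the effect evolves, which the protocol does not say. At ρ = 0.5 with an effect of 0.5 SD fading to zero by week 20, week-8 ANCOVA has 57% power and the ANOVA group effect on changes 23%. With the effect sustained at 0.5 SD the order reverses, 59% against 67%. Adjustment wins only when the same contrast is compared.
- **Baseline discarded.** Changes use the baseline, though inefficiently.
- **Hypnotic use.** Section 3.3 admits patients "Independent of hypnotics, or using a minimal maintaining dose of hypnotics", which suggests a second covariate. No gain from it has been shown, and Section 8.3 gives no time points for the dose. It is optional.
- **Unknown correlation.** Entry above a PSQI threshold narrows the baseline range and tends to lower the correlation. At 0.3 the gain over a final-score t test is only 7 to 9%.
- **Left to the SAP.** Covariates are often specified there, and an SAP may exist. But Section 11 already names the tests, and as named they are unadjusted. If an SAP adds the covariate, the protocol needs only to be brought into line.

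None of this removes the like-for-like gain.

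**Conclusion.** The concern holds as a matter of precision. Adding baseline PSQI to the same contrast reduces its variance at any plausible correlation. The variance falls by 9% to 49% against the final-score t test and by 15% to 35% against the change-score t test for ρ from 0.3 to 0.7, slightly less after the cost of estimating the slope. These figures rest on an assumed correlation, equal SDs and complete data; the result for the average over visits also assumes equal correlation between visits. The protocol supplies none of these quantities.

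The planned analyses remain valid, and in a feasibility pilot of 60 the consequence is limited. The documents do not support a finding of bias, of a missed end-of-treatment target, or of general superiority of a week-8 contrast. This is a worthwhile improvement at almost no cost, not a defect that undermines the trial.

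**What to change.** Reword Section 11 along these lines:

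- Analyse PSQI global score and each domain at weeks 8, 12, 16 and 20 with a repeated-measures mixed model. Fixed effects are arm, visit and arm-by-visit, with the baseline value of the same score as covariate.
- Report the AA minus SAA difference with its 95% CI at each visit, or for one contrast that the sponsor names in advance. Week 8 and the average over the four visits are both reasonable; the choice is the sponsor's.
- For other continuous outcomes with a baseline value, such as the laboratory parameters at week 20, replace the t test by ANCOVA on that value.
- Adjustment for baseline hypnotic use may be added but is not needed for this point.

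The cost is wording in one section. Baseline PSQI is already collected, and no visit, patient or procedure is added.
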